## Background

Gastroesophageal reflux disease (GERD) is a condition in which stomach contents flow back into the esophagus or oral cavity, causing discomfort or complications [1]. Typical symptoms of GERD include heartburn or acid regurgitation. Extraesophageal symptoms may include chest pain, coughing, and hoarseness. These symptoms can worsen with weight gain [2–5]. The prevalence of GERD varies worldwide, ranging from 2.5 to 33.1%. Since 1995, there has been a rising trend in its incidence, particularly in North America and East Asia [6]. Consequently, there is a growing interest in its ongoing treatment and management due to the societal cost associated with reduced quality of life [7, 8]. Standard treatments for GERD include weight loss, proton pump inhibitors (PPIs) like omeprazole, rabeprazole (RPZ), and esomeprazole, histamine-2 receptor antagonists (H2RAs), prokinetics, and occasionally anti-reflux surgery [4, 5].

GERD is categorized into erosive esophagitis (EE) and non-erosive reflux disease (NERD) based on the presence or absence of esophageal mucosal damage on endoscopy. A study showed that the response rates to 4 weeks of PPI therapy were 37% for NERD and 56% for EE, indicating lower effectiveness in patients with NERD [9]. GERD often follows a chronic course with symptoms recurring upon treatment discontinuation. Thus, effective treatments and lifestyle modifications are crucial [10]. The causes and mechanisms of GERD symptoms vary, leading to cases where PPIs do not yield improvement, known as refractory GERD (rGERD) [11]. Patients unresponsive to once-daily PPI therapy might benefit from twice-daily dosing and long-term maintenance therapy [12]. Although long-term PPI use is essential for GERD, concerns about associated adverse effects, such as *Clostridium difficile* infection, bone fractures, and acute kidney injury, have been raised [13, 14]. rGERD involves diverse pathophysiologies, including acid nature, reflux, delayed gastric emptying, motility inefficiencies, and cytochrome P450 (CYP) isoenzyme, CYP2C19, genetic polymorphism. To alleviate symptoms, a combination of PPIs and prokinetic agents is often used [15–19]. Complementary and alternative therapies, including botanical drugs, are actively researched as promising GERD management options [20]. If the therapeutic effects of these botanical drugs on GERD are verified, they could potentially reduce overall PPI dosage when used alongside or as an alternative to PPIs.

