#### Primary outcome

##### Frequency Scale for the Symptoms of GERD (FSSG)

In addition to the typical symptoms of GERD, the FSSG includes an assessment of dyspeptic symptoms, such as bloating and postprandial fullness. Participants will be required to rate how often they experience each of the 12 symptoms on a scale of 0 (never) to 4 (always), with a total of 48 points, which will be summed by dividing the symptoms into two categories: acid reflux and dysmotility [36]. The FSSG will be measured at all visits except the screening visit, and the change in the FSSG score from baseline to 4 weeks will be calculated. The improvement between the baseline and follow-up period will be compared between the groups to determine the persistence of the treatment effect. In addition, the proportion of participants with no GERD symptoms at one-week recall, referred to as a treatment responder, will be compared between the groups.

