### Sample size calculation

The results of previous study were used to determine the non-inferiority margin required to calculate the sample size [42]. The upper limit of the 95% confidence interval for the mean difference in the degree of improvement of FSSG between the test and control groups after 4-week treatment was estimated to be -8.29. Assuming a significance level of 2.5%, a statistical power of 90%, and a 1:1 allocation ratio, 86 participants (43 per group) would be required to account for a dropout rate of 30%, considering the larger standard deviation of 9.8.

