### Statistical analysis

Statistical analyses will be performed by an independent statistician using the statistical software IBM SPSS Version 25.0 (IBM Corp.). The study will use per-protocol set (PPS) as the primary method of analysis, with full analysis set (FAS) analysis as secondary confirmation, if necessary. The PPS analysis will be applied to patients who are fully compliant with the protocol. In this study, data from patients who comply with IP (≥ 80%), assess the primary efficacy endpoint, and complete the study without major protocol violations will be included in the analysis. The FAS population will consist of data from patients who meet the inclusion criteria, have taken the IP at least once, and have at least one endpoint measurement. The safety analyses set will include all data from patients who received at least one dose of IP after randomization.

For the comparative evaluation of demographic or clinical characteristics between groups, two-sample t-tests will be performed for continuous data, and the chi-squared test or Fisher's exact test will be used for dichotomous data. If significant differences are found between the groups, one-way analysis of covariance will be conducted for continuous data, and logistic regression will be performed for dichotomous data to correct the imbalance.

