The basic principle of statistical analysis for the efficacy endpoints is the comparison of data between the two groups after the 4-week treatment intervention. For the efficacy endpoint at week 4, a one-sided 97.5% confidence interval will be calculated to confirm non-inferiority (*p* < 0.025) by determining the difference in mean changes of the questionnaire score between the treatment and control groups. All measurements will be presented as mean ± standard deviation or as percentages (n %). Mean comparisons between groups will be conducted using a two-sample t-test as a parametric method or a Mann–Whitney test as a non-parametric method. Differences within each group between baseline and measurements after a specific period will be analyzed using either the paired t-test or the Wilcoxon signed-rank test. Repeated measures will be analyzed to compare the changes in the mean value of the same variable measured over time between the two groups. For safety assessments, the incidence of adverse and serious adverse events will be calculated and tested by group using the chi-square test or Fisher's exact test. Differences in effectiveness between subtypes, where applicable, will be determined by analysis of variance, considering participant characteristics (such as sex and age), GERD classification (including EE and NERD), previous PPI therapeutic dosage, GERD pattern identification, and other clinical characteristics.

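### Covariate adjustment is triggered by baseline significance tests, and baseline FSSG is not a pre-specified covariate for the primary difference in mean change

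*Protocol article*

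**What the plan says.** All of this is in the Methods of the protocol article.

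- **Endpoint.** The primary outcome section states that "the change in the FSSG score from baseline to 4 weeks will be calculated". Baseline FSSG therefore enters by subtraction.
- **Primary comparison.** The Statistical analysis section says "a one-sided 97.5% confidence interval will be calculated to confirm non-inferiority", obtained "by determining the difference in mean changes of the questionnaire score between the treatment and control groups". No covariate is named.
- **Adjustment.** The same section tests demographic and clinical characteristics between the arms (t-test, chi-squared or Fisher) and continues: "If significant differences are found between the groups, one-way analysis of covariance will be conducted for continuous data". Logistic regression is the counterpart for dichotomous data. The characteristics to be tested, the significance level and the covariates are not named.
- **Accompanying tests.** A later general sentence reads "Mean comparisons between groups will be conducted using a two-sample t-test as a parametric method or a" Mann-Whitney test as the non-parametric alternative.

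**The concern.** In a randomised trial, any baseline difference between arms arose by chance. A test of that difference says nothing about whether the variable predicts FSSG at week 4, which is the only reason to adjust for it. Using the test as a gate has three consequences:

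- The estimator behind the non-inferiority interval is settled only after the baseline data have been compared by arm.
- A baseline FSSG gap that falls short of significance stays in the result. Subtracting baseline removes the effect of a gap fully only if the correlation between visits is 1. Otherwise regression to the mean moves the difference in mean change.
- In most trials the precision that baseline FSSG could supply is not used, although the score is collected anyway.

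The trigger is not confined to FSSG. If, for illustration, 10 independent characteristics were tested at 5%, at least one would be significant by chance in 1 − 0.95^10 = 40% of trials, whether or not it had any bearing on outcome.

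**Working it through.** **Inputs from the article (Sample size calculation; Statistical analysis).** Margin 8.29 in absolute value (printed as −8.29), SD 9.8, one-sided 2.5%, power 90%, 1:1 allocation, dropout 30%, total 86.

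**Assumptions.** True difference 0. The correlation ρ between baseline and week-4 FSSG is not given, so 0.3, 0.5 and 0.7 are used. SDs are equal at the two visits. The article does not say which SD the 9.8 is; both readings are shown where it matters.

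**1. The plan's own figure.** n per arm = 2 × (1.960 + 1.282)² × 9.8² / 8.29² = 29.4, so 30. Then 30 / 0.70 = 42.9, so 43 per arm and 86 in total. This reproduces the stated size for an unadjusted two-sample comparison, and 30 evaluable per arm is used below.

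**2. Precision given up.** With visit SD s, the variance of change is 2s²(1 − ρ) and the ANCOVA residual variance is s²(1 − ρ²). The ratio is (1 + ρ)/2.

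| ρ | Variance ratio | Variance cut | CI narrower by |
|---|---|---|---|
| 0.3 | 0.65 | 35% | 19% |
| 0.5 | 0.75 | 25% | 13% |
| 0.7 | 0.85 | 15% | 8% |

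**3. Operating characteristics.** Simulation with 100,000 normal trials per scenario, 30 per arm and SD of change 9.8. Baseline FSSG is the only variable tested, at two-sided 5%.

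| ρ | Power: change-score t-test | Power: conditional rule | Power: ANCOVA always | One-sided type I error: conditional rule |
|---|---|---|---|---|
| 0.3 | 89.4% | 90.6% | 97.7% | 2.0% |
| 0.5 | 89.7% | 90.4% | 95.8% | 2.2% |
| 0.7 | 89.6% | 90.1% | 93.3% | 2.3% |

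The rule switches to ANCOVA in about 5% of trials. Against ANCOVA always, it loses 7.1, 5.4 and 3.2 points of power. Either fixed method has a type I error of about 2.5%.

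**4. Imbalance left in the result.** The shift in the difference in mean change is (1 − ρ) × baseline gap.

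- With baseline SD 9.8, the SE of the baseline difference is 9.8 × √(2/30) = 2.53.
- Expected absolute gap: 2.53 × √(2/π) = 2.0 points. At ρ = 0.5 the shift is 0.5 × 2.0 = 1.0 point, or 12% of 8.29.
- Largest gap that is still not significant: 2.53 × 2.002 = 5.07 points. At ρ = 0.5 the shift is 2.5 points, or 31% of 8.29. At ρ = 0.7 and 0.3 it is 1.5 and 3.5 points.
- If 9.8 is instead the SD of change, the baseline SD is 9.8/√(2(1 − ρ)) = 8.3, 9.8 and 12.7 at ρ = 0.3, 0.5 and 0.7. The worst-case shifts are then 3.0, 2.5 and 2.0 points.
- About 27% of trials would have a gap between 1 SE and the significance cut-off, and so would go uncorrected.

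**The case against.** The best defence is that the design delivers what it promises. The conditional rule keeps the stated 90% power and does not exceed the nominal 2.5% in simulation. The sample size reproduces, and the change-score estimator is unbiased over randomisations. The 2.5-point shift is the edge of the non-significant range; the typical shift is about 1 point. All of that stands, and it makes this a matter of efficiency and pre-specification, not of validity.

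A reader might infer more than the article supports:

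- **That the primary comparison ignores baseline FSSG.** It does not: the endpoint is change from baseline, and ANCOVA is possible. The accurate statement is that baseline FSSG is not a pre-specified covariate.
- **That an open choice between t-test and Mann-Whitney could flip the verdict.** The non-inferiority criterion is fixed separately as an interval for the difference in mean changes, and nothing says a rank test would replace it. A rule for choosing the accompanying test may sit in an analysis plan that is not shown. What can be said is that a standard Mann-Whitney test gives no interval for a difference in means, so it cannot carry the margin comparison.
- **That randomisation is unstratified despite different prognosis in EE and NERD.** The article is silent on stratification. Its figures, "the response rates to 4 weeks of PPI therapy were 37% for NERD and 56% for EE", describe response to PPI therapy, whereas this trial enrols people still symptomatic after it.
- **That the subtype analysis is wrong.** The sentence "Differences in effectiveness between subtypes, where applicable, will be determined by analysis of variance" does not exclude a treatment-by-subtype term, and model terms are commonly left to the analysis plan.

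The possible existence of an analysis plan does not excuse the gate itself. It is a rule the article states outright, not a detail it omits.

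**Conclusion.** The point holds in limited form. Making adjustment depend on baseline significance is poor practice in a randomised trial. It lets the data choose the primary estimator, leaves non-significant FSSG imbalance in the estimate, and forgoes about 3 to 7 points of power that already collected data would supply. The expected effect of imbalance is about 1 FSSG point at correlation 0.5, set against a margin of 8.29.

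The sizes rest on the assumed correlation, equal visit SDs, normal data, 30 evaluable per arm and the reading of 9.8. The simulation tested baseline FSSG alone, so it does not describe the rule when many characteristics can trigger adjustment. It gives no ground for claiming an inflated overall type I error, and the planned 86 participants are not in question. The change should be made, but the trial is valid without it.

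**What to change.** - Make the primary analysis an ANCOVA of week-4 FSSG (or its change) on treatment and baseline FSSG, whatever the baseline comparison shows. EE/NERD is an optional further covariate, to be fixed in advance if used.
- Read non-inferiority from the one-sided 97.5% confidence interval for the treatment effect in that model.
- Drop baseline significance tests as a trigger; describe baseline characteristics by arm instead.
- Keep any Mann-Whitney test as supportive only.
- Put any treatment-by-subtype term in a separate exploratory model, because including it in the primary model changes the meaning of the treatment coefficient.

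**Cost.** No new data and no change in sample size: baseline FSSG is already measured and ANCOVA is already among the planned methods. Recruitment is under way under an approved protocol, so the change needs an amendment, made before unblinding. If an analysis plan already fixes baseline FSSG as a covariate, the protocol wording should be brought into line with it.

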**Methods:**

A total of 86 participants with refractory GERD (rGERD) will be randomized in a 1:1 ratio to the treatment [YGJ and RPZ (10 mg/d)] and control groups [double-dose RPZ (20 mg/d)] for 4 weeks of treatment (weeks 0–4) followed by 4 weeks of follow-up (weeks 4–8). The Frequency Scale for the Symptoms of GERD will be analyzed for the primary endpoint. Reflux Disease Questionnaire, Reflux Symptom Score, GERD-Health Related Quality of Life, Overall Treatment Evaluation, Spleen Qi Deficiency Questionnaire, Damum Questionnaire, and dyspepsia Visual Analogue Scale will be used to evaluate treatment effects on GERD related symptoms and quality of life and to compare treatment effects by subgroups. Safety tests will be analyzed by investigating adverse events.

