### Outcome measures

#### Demographic and baseline information

Demographic information, medical history including medications and surgery, and alcohol consumption will be examined in detail. The GERD-related information will be investigated to determine the timing of symptom onset and diagnosis, upper endoscopy findings, symptom severity, and treatment history. Participants will also be categorized into five subtypes using a 32-item questionnaire of standard tools for the pattern identification of GERD based on their GERD-related symptoms and health conditions: liver-stomach disharmony, middle qi deficiency counterflow, qi depression phlegm obstructing, stomach yin insufficiency, and spleen-stomach dampness-heat patterns [35].

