Assessment and quantification of GERD symptoms are important endpoints for efficacy validation. In this study, the FSSG score was selected as the primary outcome by expert consensus to assess the severity and frequency of heartburn and acid reflux, which are typical symptoms of GERD, and to evaluate responders. Based on a previous study that used the FSSG as a primary outcome, we calculated the optimal sample size for hypothesis testing [42]. RDQ, RSS, and dyspepsia VAS were selected as secondary variables to evaluate the specific discomfort of typical and atypical GERD symptoms simultaneously, and GERD-HRQL, a disease-specific questionnaire, will be used to evaluate the quality of life in patients with GERD. In traditional medicine, the indications for YGJ include the patterns of Spleen Qi Deficiency and Damum, characterized by symptoms of general weakness, dyspepsia, and throat discomfort [40, 41]. Thus, the SQDQ and DQ were evaluated to assess the symptom improvement effects of the combination treatment and to compare the differences in efficacy across subtypes. The OTE was selected as an assessment tool to evaluate the patient's impression of the treatment for overall symptom changes, which is most important in the clinical field.

In conclusion, the primary purpose of this study is to clinically confirm the feasibility of substituting YGJ for dose escalation of PPIs. This substitution will serve as a basis for the retrospective exploration of its mechanisms of action and be considered as a treatment option, other than PPIs, to improve GERD symptoms. One limitation of this study is that it is a single-center study specific to Koreans; therefore, it may be difficult to generalize the results to other populations worldwide. However, as the first double-blind, randomized clinical trial to evaluate the efficacy and safety of a cooperative and integrated approach of both Western and botanical drugs in GERD treatment, the results of this study will clarify and strengthen the objective clinical evidence for the effectiveness of combination therapy for rGERD. By expanding the effective treatment options and management methods for GERD through the use of botanical drugs, this approach can contribute to the development and implementation of clinical guidelines. These guidelines will provide valuable medical information to healthcare professionals and help improve public health.

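### As written, the subgroup ANOVA names neither treatment arm nor an arm-by-subtype interaction, so it may show only which patients improve more, not where the treatment effect differs

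*Protocol article*

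**What the plan says.** The Statistical analysis section says: "Differences in effectiveness between subtypes, where applicable, will be determined by analysis of variance, considering participant characteristics". The characteristics it then lists are sex, age, EE or NERD, and finally "previous PPI therapeutic dosage, GERD pattern identification, and other clinical characteristics", so the list has no end point. Pattern identification has five levels. Under Demographic and baseline information the article says: "Participants will also be categorized into five subtypes using a 32-item questionnaire".

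The aim is given in two other places. The Methods paragraph of the Abstract says that the secondary questionnaires will be used "to compare treatment effects by subgroups". The Discussion says that two of them, the SQDQ and the DQ, serve "to compare the differences in efficacy across subtypes".

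The paragraph that contains the subgroup sentence opens with a general rule: "The basic principle of statistical analysis for the efficacy endpoints is the comparison of data between the two groups". No treatment-by-subtype interaction is mentioned anywhere in the article.

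**The concern.** In a two-arm trial the treatment effect is a difference between arms. Whether it varies by subtype is a difference between such differences, which is the arm-by-subtype interaction. An ANOVA with subtype as its only factor tests something else, namely whether mean improvement differs between subtypes. It will tend to be significant when one subtype does better in both arms, even if the treatment makes no difference to that gap.

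Such a gap is plausible here. Both arms receive rabeprazole, and the Background cites 4-week PPI response of 37% in NERD and 56% in EE. A prognostic difference of that kind could be reported as a difference in effectiveness between subtypes. The reverse error is also possible: if the arms differ in opposite directions across subtypes, the pooled subtype means can coincide and real effect modification goes unseen.

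**Working it through.** **Plan's own figure first.** The inputs come from Sample size calculation: margin 8.29 (the size of the figure in "between the test and control groups after 4-week treatment was estimated to be -8.29"), SD 9.8, one-sided 2.5%, power 90%, 1:1 allocation, 30% dropout.

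- n per arm = 2 × (1.96 + 1.2816)² × 9.8² / 8.29² = 29.4, rounded up to 30 evaluable.
- 30 / 0.70 = 42.9, rounded up to 43 per arm, or 86 in total. This matches the plan.

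The subgroup analysis therefore has between 30 (evaluable) and 43 (all randomised) patients per arm. The article gives no figure for the subgroup analysis itself.

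**Precision of the interaction, two equal subtypes (assumed).**

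- Main comparison: SE = 9.8 × √(2/n) = 2.53 at n = 30 and 2.11 at n = 43.
- Interaction: four cells of n/2, so SE = 9.8 × √(4/(n/2)) = 5.06 at n = 30 and 4.23 at n = 43, twice the main SE.
- 95% half-width: 1.96 × 5.06 = 9.9 points, or 1.96 × 4.23 = 8.3 points.
- Normal-approximation power for an interaction of 8.29 points at n = 30: Φ(8.29/5.06 − 1.96) = Φ(−0.32) = 37%. The main comparison has Φ(8.29/2.53 − 1.96) = 91%.
- Five patterns by two arms, if even: 60/10 = 6 to 86/10 = 8.6 patients per cell.

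**What a subtype-only ANOVA would do.** The simulation used 2,000 trials per setting, SD 9.8, equal subtypes and a two-sided 5% level. The shifts are assumptions, because the article gives none. The table is for 30 per arm and shows the share of trials that are significant.

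| Assumed truth | Subtypes | ANOVA, arms pooled | ANOVA, test arm only | Interaction test |
|---|---|---|---|---|
| One subtype better by 5 points in both arms, same treatment effect | 2 | 49% | 27% | 5.3% |
| Same, 8.29 points | 2 | 90% | 62% | 4.4% |
| Same, 5 points | 5 | 20% | 11% | 5.6% |
| Same, 8.29 points | 5 | 51% | 25% | 4.6% |
| Treatment effect differs by 8.29 points, split in opposite directions across arms | 2 | 4.8% | 21% | 38% |
| Same, 16.58 points | 2 | 2.0% | 58% | 90% |
| Same, 8.29 points | 5 | 4.0% | 8% | 14% |
| Same, 16.58 points | 5 | 2.5% | 24% | 50% |

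The first four rows contain no effect modification. At 43 per arm with two subtypes, the pooled ANOVA figures for the 5- and 8.29-point shifts rise to 64% and 98%, and the interaction test stays at 5% to 6%.

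Adding arm as a factor without the interaction, and then reading the subtype effect, does not help. For two subtypes at 30 per arm it is significant in 49% and 89% of trials. It is the interaction term that answers the question.

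**The case against.** The strongest objection is that the article does not say the ANOVA is one-way, pooled over arms or run in one arm only. The term also covers a two-way model with arm, subtype and interaction. The same section specifies a one-way model where it plans covariance adjustment for baseline imbalance, and it does not use that qualifier here. The paragraph opens with comparison of the two groups as its basic principle, and the Abstract's aim can be read as explaining the subgroup sentence. The article is condensed, so the model may be set out elsewhere.

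This stands in part. A reader might infer that the planned ANOVA certainly does not test whether the treatment effect differs, and the text does not support that. What remains is that the article does more than leave a gap. It names a method and what is compared, which is subtypes, whereas the between-arm comparisons in the same paragraph say that they are between arms. Read literally, the named comparison does not answer the stated question.

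Two further inferences should not be drawn:

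- **A subtype effect is certain.** The 37% and 56% are response rates to PPI therapy from one cited study. This trial enrols patients still symptomatic after at least 4 weeks of PPI and analyses FSSG change. The figures make a prognostic gap plausible, no more.
- **Subgroup results are meant for guidelines.** The Discussion's remark on guidelines concerns the combined approach as a whole and does not mention subgroup findings.

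It is also fair to say that the simulated rejection rates depend on assumed shifts, and that the SEs describe the limits of the recommended test rather than the error in the planned one.

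**Conclusion.** The point holds as a defect of specification. The subgroup sentence fixes an ANOVA between subtypes, names no arm and no interaction, and leaves its factor list open. Followed literally, it can turn a prognostic difference into an apparent difference in effectiveness. That happened in 49% to 90% of simulated trials with two equal subtypes, 30 per arm and assumed shifts of 5 to 8.29 points. When pooled over arms, it can also miss effect modification that runs in opposite directions.

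The correct test has little power at this size. With SD 9.8 and two equal subtypes, the interaction SE is about 5.1 points at 30 per arm or 4.2 at 43, and power for an 8.29-point interaction is about 37% at 30 per arm. Unequal subtypes would be less precise still. Any subgroup result is therefore exploratory.

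This is a secondary analysis. The primary non-inferiority test and the sample size do not change. If the sponsor already intended a two-way model with interaction, one sentence that says so settles the model question.

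**What to change.** Rewrite the subgroup sentence to say four things:

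1. Each subgroup analysis fits a linear model (two-way ANOVA or ANCOVA) of FSSG change with arm, subtype and the arm-by-subtype interaction. The interaction, not the subtype effect, is the test of differing treatment effect.
2. The between-arm difference with its 95% CI is reported within each level of each subgroup.
3. The factor list, including any cut-points for age and previous PPI dosage, is closed before unblinding. Which factors to keep is the sponsor's choice.
4. All subgroup results, including the five patterns, are labelled exploratory.

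The cost is wording only, with no new data and no change in sample size. The downside is fewer apparent subgroup findings and wide intervals for those that are reported.
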